**Enrolled prior to March 1, 2020**	
No preference between interventions	Randomly assigned to one of the four study arms: three interventions without waitlist and the waitlist arm, with a 1:1:1:1 ratio.
Preferred two interventions equally and over the third intervention	Randomly assigned to one of the two interventions with a 1:1 ratio, and then, a fraction was randomly assigned to the waitlist arm, with a 3:1 non-waitlist vs waitlist ratio for MBSR and stress proofing and a 5:4 non-waitlist vs waitlist ratio for the Daily Examen (DE was preferred by more participants and this allowed the same number of participants to be randomized into each study arm).
Preferred one intervention among the three	Assigned to their preferred intervention and combined with participants with two top preferences who had been randomized to that intervention, and then randomly assigned to non-waitlist vs waitlist arms, with a 3:1 non-waitlist vs waitlist ratio for MBSR and stress proofing and a 5:4 non-waitlist vs waitlist ratio for the Daily Examen.
Any of the above scenarios and are part of a married or cohabitating couple who both meet study criteria and enrolled	To avoid spillover effects, each couple was treated as if they were one person, i.e., assigning both spouses to the same intervention and randomizing them into a non-waitlist vs waitlist arm. When a couple had different preferences, one preference was randomly chosen as the couple’s preference.
Seven clergy with an established meeting group (a covenant group)	The seven clergy jointly chose a single preferred intervention and were randomized together to the non-waitlist vs waitlist arm.

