### Analysis

#### Statistical analysis plan

##### Power analysis

A baseline average C-SOSI score of 0.92 (SD = 0.46) and average 12-week follow-up scores of 0.7 (SD = 0.58) for MBSR, 0.55 (SD = 0.36) for stress proofing, and 0.51 (SD = 0.38) for Daily Examen are expected based on study pilot data. Given an alpha of 0.0167 (based on a Bonferroni correction to hypothesis tests for the effects of 3 interventions on C-SOSI scores), a per-arm sample size of 195 for MBSR, 40 for Daily Examen, and 47 for stress proofing will yield 80% power to detect a between-arm difference in the means at 12 weeks of 0.22 for MBSR, 0.37 for stress proofing, and 0.41 for Daily Examen for a two-sample *t*-test with unequal variances, allowing for a loss-to-follow-up of 20% and a design effect of 1.3 (corresponding to an ICC of 0.027 and average cluster size of 12) to account for clustering caused by the group-based intervention delivery.

Previous literature recommends that medium effect size (difference in means/standard deviation) for HRV be defined as 0.50. A per-arm sample size of 140 will yield 80% power to detect an effect size of 0.50 for a two-sample *t*-test with an alpha of 0.0167, allowing for a loss-to-follow-up of 20% and a design effect of 1.3 to account for the group-based intervention delivery. All power analyses were performed using the PASS 2021 software.

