##### Data analysis

All primary and secondary study outcomes are measured on continuous scales and will be reported with mean estimates and 95% confidence intervals using the intention-to-treat principle with reference to the waitlist vs non-waitlist for participants randomly assigned prior to March 1, 2020. Linear mixed models will be specified with fixed effects for time and intervention status, and partially clustered random effects for the non-waitlist arms will be used to account for the clustering caused by workshop-level intervention delivery that affects participants in the intervention condition vs the un-clustered structure for those in the waitlist condition. Distributions of residuals will be examined to confirm that modeling assumptions are met. Models with adjusted and unadjusted estimates will be specified, with adjustment covariates such as age, sex, and bi-vocational status chosen prior to unblinding and finalization of the analysis plan and sensitivity analyses to include any additional relevant covariates that are identified. We will include race and ethnicity contingent upon there being meaningful heterogeneity. We may choose to adjust for baseline stress level to improve the precision of the treatment effect. In addition, for the models evaluating HRV, an a priori decision was made to include baseline sex, age, caffeine intake, alcohol consumption, body mass index, and physical activity as covariates given the influence that these variables exert on HRV [35]. For the primary outcome of stress symptoms, *p*-values will be calculated for the 12-week differences for each of the 3 interventions vs waitlist and will be adjusted for multiple comparisons using the Benjamini-Hochberg correction [36].

The effects of preferences on intervention estimates will be ascertained by introducing binary indicators for receipt of intervention preference vs assignment by random choice, which will be interacted with intervention indicators. Because this study is not powered to detect such interaction effects, the analytic focus will be on the magnitude of interaction effects and their 95% confidence intervals.

We will perform sensitivity analyses adjusting for any influential covariates (e.g., baseline financial stress, depressive symptoms, marital status; see Table 2) that are imbalanced by chance between waitlist and non-waitlist arms.

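### Couples and a seven-person covenant group were randomised as whole units, but the stated model has no term for these units and treats the waitlist as un-clustered; the effect on standard errors is probably small.

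*Protocol article*

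**What the plan says.** Three parts of the protocol article bear on this.

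- **Randomization and blinding, Table 1 (enrolled before March 1, 2020).** For couples, "each couple was treated as if they were one person, i.e., assigning both spouses to the same intervention". The same row then gives the pair a single allocation, which it describes as "randomizing them into a non-waitlist vs waitlist arm". For the covenant group, "The seven clergy jointly chose a single preferred intervention and were randomized together to the non-waitlist vs waitlist arm". Both kinds of unit could therefore fall in either arm.
- **Data analysis.** The linear mixed model is described thus: "partially clustered random effects for the non-waitlist arms will be used to account for the clustering caused by workshop-level intervention delivery". This is set against "the un-clustered structure for those in the waitlist condition". Each of the three interventions is compared with the waitlist, which the Study arms section describes as a single arm.
- **Power analysis.** A design effect of 1.3 (ICC 0.027, average cluster size 12) is applied and attributed to group-based delivery alone.

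The article names no random effect, robust variance or sensitivity analysis for couples or the covenant group.

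**The concern.** The analysis should respect the unit that was randomised. Table 1 gives a reason to expect dependence: spouses were kept together because of possible spillover, and the seven colleagues already met as a group. If such people sit in the waitlist, the stated model counts them as independent and overstates the information in that arm.

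All three interventions are compared with that one waitlist. An understated waitlist variance therefore enters every comparison with it, for stress symptoms, HRV and anxiety alike. Confidence intervals would be too narrow and p-values too small.

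In the intervention arms the gap is less clear. Where members of a unit attend the same workshop, the workshop effect absorbs part of their dependence. Table 1 assures couples the same intervention but does not say that they share a workshop.

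**Working it through.** **1. The plan's own figures reproduce.** Inputs from Power analysis: alpha 0.0167 (taken as two-sided), power 80%, comparator SD 0.46, intervention SDs 0.58, 0.36 and 0.38, differences 0.22, 0.37 and 0.41, design effect 1.3, loss 20%.

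- Design effect: 1 + (12 − 1) × 0.027 = 1.297, about 1.3.
- MBSR: the Welch t-test needs 120 per arm; 120 × 1.3 = 156; 156 / 0.8 = 195.
- Stress proofing: 28 × 1.3 = 36.4, so 37; 37 / 0.8 = 46.25, so 47.
- Daily Examen: 24 × 1.3 = 31.2, so 32; 32 / 0.8 = 40.
- HRV: 86 × 1.3 / 0.8 = 139.75, so 140.

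All match the article. None contains an allowance labelled for couples or the covenant group.

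**2. Design effect from randomising whole units.** For an arm of N people with units of size m, it is 1 + ICC × Σm(m − 1) / N. The covenant group adds 7 × 6 = 42 to the sum, each couple adds 2 × 1 = 2, and single people add 0. The stated model sets this to 1 in the waitlist.

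Covenant group alone in the waitlist, ICC 0.027 to 0.3:

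- N = 40: 1.028 to 1.315
- N = 100: 1.011 to 1.126
- N = 195: 1.006 to 1.065

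If instead the waitlist holds only couples, say 5 of them, its design effect is between 1 + 0.027 × 10 / 195 = 1.001 and 1 + 0.3 × 10 / 40 = 1.075.

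**3. Standard error of the treatment difference.** With equal arms and equal variances, the ratio of true to model SE is the square root of the mean of the two arms' design effects. The true two-sided error is 2 × (1 − Φ(z / ratio)), where z is the nominal critical value. The covenant group is placed in the waitlist and couples in both arms. Workshop clustering is left out, and none of the couples' dependence in the intervention arm is taken as absorbed by it.

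| Assumed case | Waitlist | Intervention | SE ratio | 0.05 becomes | 0.0167 becomes |
|---|---|---|---|---|---|
| 195 per arm, 2 couples per arm, ICC 0.027 | 1.006 | 1.001 | 1.002 | 0.0504 | 0.0169 |
| 100 per arm, 5 couples per arm, ICC 0.1 | 1.052 | 1.010 | 1.015 | 0.0536 | 0.0184 |
| 40 per arm, 10 couples per arm, ICC 0.3 | 1.465 | 1.150 | 1.143 | 0.0865 | 0.0364 |

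Middle row written out: waitlist 1 + 0.1 × (42 + 10) / 100 = 1.052; intervention 1 + 0.1 × 10 / 100 = 1.010; √((1.052 + 1.010) / 2) = √1.031 = 1.015.

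Arm sizes, numbers of couples and within-unit ICCs are assumptions. The range of N spans the planned per-arm sizes of 40 to 195. The value 0.027 is the article's only ICC, and it was given for workshops.

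**The case against.** The best defence is that the un-clustered wording only contrasts the waitlist with the workshops, and that a condensed article may leave a variance term for a few linked participants to the analysis plan. The first half is a fair reading of the sentence. But the article does more than stay silent: it says where the random effects go and gives the waitlist none, although its own Table 1 allows whole units to be placed there.

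Other objections stand and limit the point.

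- There is one covenant group, and it is in one arm only. With one chosen intervention, the ratios in Table 1 give it a 1 in 4 chance of the waitlist (3:1) or 4 in 9 (5:4). An intervention arm was the likelier outcome, and then only couples could affect the waitlist.
- In the intervention arms, it is not in itself an error that unit and workshop effects are not separated. A valid standard error does not require it.
- A unit variance would rest on one group of seven and an unknown number of couples, so it would be poorly estimated.

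A reader might also infer that the seven form a large share of a small control group, by splitting the waitlist by preferred intervention. The documents do not support this. They describe one waitlist arm compared with each intervention, specify no comparison within preference strata, and give no waitlist size. Table 1 says the allocation ratios were chosen to equalise numbers across arms.

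**Conclusion.** The point holds in conditional form. If at least one couple or the covenant group is in the waitlist, and within-unit correlation is positive, the stated model understates the standard error in all three comparisons with the waitlist.

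The size is probably small. Under the assumptions shown, the understatement is about 5% or less in most combinations and 1.5% in the middle case. It reaches about 14% only when a 40-person arm, 10 couples per arm, an ICC of 0.3 and the covenant group in the waitlist all coincide.

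Two stronger conclusions do not follow. The article does not establish that the standard errors are in fact too small, since the covenant group's arm, the number of couples and the correlation are not given. Nor is the sample size shown to be inadequate. The 1.3 inflation was applied per arm, including to a waitlist with no workshops, and it exceeds the waitlist's unit design effect in every case examined with 100 or more per arm (highest 1 + 0.3 × 62 / 100 = 1.186). The fault is in the analysis model.

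**What to change.** - Define a randomisation-unit identifier: covenant group, couple or single person.
- Account for it in both arms alongside workshop, by a random intercept or by cluster-robust standard errors with a small-sample correction.
- Amend the Data analysis text to say that the waitlist has no workshop clustering but does have clustering by randomisation unit.
- Add a sensitivity analysis without the covenant group.

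The cost is low. Unit membership is known from allocation, so no new data are needed. Intervals widen slightly. The unit variance will be weakly estimated because most units are single people, and a single random intercept imposes one common correlation on spouses and colleagues. The sensitivity analysis is therefore a useful complement.

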**Enrolled after March 1, 2020**	
All enrollees after March 1, 2020, with no preference, two equal preferences, or one preference, and whether a clergy couple or not	Participants answered treatment preference survey items, but regardless of their answers, self-selected the intervention with intervention dates they most wanted from the full list of workshop options. None was randomized to the non-waitlist vs waitlist arms; they all were assigned to non-waitlist.

#### Study arms: non-waitlist interventions and waitlist

This trial includes three non-waitlist study arms (mindfulness-based stress reduction, Daily Examen, and stress proofing) and one waitlist arm that includes two conditions: first providing control data and then participating in any intervention condition. Originally, participants were to be trained in small workshop formats delivered across NC between April 2020 and May 2021. Due to the global pandemic, all workshops were converted to online delivery formats and delivered during the same anticipated months. Interventions will be delivered in small groups of 10–25 participants. Survey data will be collected online, and HRV data will be collected by the participants in their respective personal settings.

##### Mindfulness-based stress reduction (MBSR)

MBSR teaches several different kinds of meditation and attitudes. The specific course for this study is a synchronous web-based video platform course with certified instructors from Duke Integrative Medicine and content based on Jon Kabat-Zinn’s model [16, 17]. It includes exercises in awareness of breath, body scans, walking meditation, “choiceless” open awareness, loving kindness meditation, and bringing awareness to the present moment. The course consists of 8 weekly sessions confined to study participants held via video conference with meditation instruction, periods of guided practice, and group discussion. Participants are also offered a 4-h online “day of mindfulness” which includes both participants and community members not enrolled in the study.

##### The Daily Examen (DE) prayer practice

The Daily Examen is a Jesuit reflective prayer practice that was first developed by Ignatius of Loyola and widely practiced by Christians from many traditions. We used a modern adaptation of the Daily Examen [18].

The Daily Examen guides the person through a five-step prayer:
Become aware of God’s presence.Review the events of the past 24 h, recalling 2–3 things for which you are grateful.Review the events of the past 24 h, guided by the Holy Spirit, noticing where you experienced God’s presence.Review what stands out and pay attention to what emotions arise. With the guidance of the Holy Spirit, pray through these emotions, noticing which are drawing you closer to God or pulling you away from God.Look forward to the next 24 h. What is the one thing you should do? Where do you need God’s assistance?

The Daily Examen is designed to help the supplicant reflect on positive emotions, move past negative emotions, and align their work with God’s work. Instructors trained in Ignatian spirituality and regular practitioners of the Daily Examen developed workshop content that included three occasions of practicing the Daily Examen, lecture instruction, and small group discussion. Topics covered include a history of Ignatian spirituality, the emotions and the spiritual life, and the practicalities of developing a daily prayer practice. We asked the participants to conduct the Daily Examen as a daily practice, requiring a 10–15-min commitment for 6 months following their workshop. Participants were also offered the opportunity to meet with their instructors in an online small group format 2 and also 6 weeks following their workshop to address any issues arising from their practice.

##### Stress proofing (SP) inoculation combination

Stress proofing is a set of stress reduction skills with aspects of stress inoculation training [19], selected and organized by the founder of an organization called NC Systema. The founder designed and led a weekly, synchronous, web-based workshop for 4 weeks. Consistent with stress inoculation training, the workshop began with education on the stress response and physical awareness of one’s own stress response [19, 20]. The training diverges from traditional stress inoculation training and goes on to focus on physical activities to undo the stress response. These activities include walking with diaphragmatic breathing, triangle and rectangle breathing, tension control, stretching, and massage. Stress inoculation training is discussed, and participants are encouraged during periods of less stress to allow themselves a degree of physical discomfort to learn to tolerate discomfort in the future [21]. The training recommends a variety of beneficial lifestyle practices, including prioritizing nutrition and sleep and disengaging from technology for several hours before sleep. The daily practice plan emphasized stress awareness and diaphragmatic breathing, with encouragement to try the lifestyle adjustments for a week at a time.

##### Waitlist condition

Participants allocated to the waitlist arm will undergo a 24-week waiting period with the purpose of providing control data, during which they will respond to surveys (0, 12, and 24 weeks). Those who are eligible will also provide a 48-h continuous ambulatory heart rate recording at 0 and 12 weeks. Upon completing the waiting period, participants will be informed that they can update their intervention preference and receive that preferred intervention while providing intervention data.

We recognize that a waitlist control condition sets a “low bar” for evaluating efficacy among interventions [22]. We decided not to use an active control condition because two of our three stress management interventions have not been evaluated as a strategy to improve stress symptoms relative to a no-treatment control group, the recommended first step in intervention evaluation. As such, it is premature to invest considerable resources and compare the Daily Examen and stress proofing to an active control before demonstrating efficacy over a waitlist control group.

#### Qualification of interventionists

Instructors for each of the three interventions were hired based on their certifications and knowledge of the specific content area. Mindfulness-based stress reduction instructors are certified instructors who have been vetted and hired by Duke Integrative Medicine’s MBSR program. Stress proofing is delivered by the founder of a North Carolina-based health coaching business. While the program has been offered to a variety of local employers, significant changes were made to it to adapt it to a clergy population. The Daily Examen instructors are certified spiritual directors trained in Ignatian spirituality with experience working with clergy and religious professionals.

### Study measures (see Table 2)

#### Primary outcomes

The *Calgary-Symptoms of Stress Inventory* (C-SOSI) is a 56-item, 8-subscale measure of self-reported stress symptoms [23]. We included the subscales of anger (8 items), muscle tension (8 items), cardiopulmonary arousal (6 items), neurological/gastroenterological (10 items), and cognitive disorganization (9 items) that total 41 items. Validation studies have shown convergent validity with specific subscales and overall divergent validity with anxiety [23]. Response options for each item range 0–4. We will use continuous mean scores of all subscales combined; higher mean scores indicate worse symptoms.

**Table 2 Tab2:** Measures by study objective and time point

Measure	Objective^a^	At consent	0 weeks^b^	12 weeks	24 weeks
**Primary outcomes**					
Calgary Symptoms of Stress Inventory (adapted)	1, 3, 4		X	X	X
48-h ambulatory heart rate	1, 4		X	X	
**Secondary outcome**					
General Anxiety Disorder-7	2, 3, 4		X	X	X
**Other pertinent measures**					
Gender, age, race, Hispanic ethnicity, bi-vocational status	Covariates for primary, secondary, and exploratory analyses		X	X	X
Godin-Shephard Leisure-Time Physical Activity Questionnaire, body mass index, caffeine intake, alcohol consumption	Additional covariates for HRV analyses		X	X	X
Preference for online vs in-person interventions, marital status, children living at home, clergy appointment	Covariates for sensitivity analyses		X		
Financial stress, Patient Health Questionnaire-8 (depressive symptoms), marital status, number of hours worked per week as a clergy, morale of congregants	Covariates for sensitivity analyses		X		
Treatment Acceptability and Preferences Scale	Inform their preference decision; covariate for sensitivity analyses	X			

^a^See the “Research objectives” section in the manuscript

^b^Zero weeks for controls; immediately pre-intervention for the intervention group

#### Heart rate

A subset of participants will be provided with an ambulatory heart rate monitoring device to wear for a 48-h period during week 0 and week 12, during which time participants proceeded with their usual daily routines, including exercising, bathing, and sleep activities.

Heart rate will be measured using continuous electrocardiographic (ECG) recording sampled at a rate of 1000 Hz and used to calculate *heart rate variability*. Participants will be fitted with an eMotion Faros 180 ambulatory heart rate recording device (Bittium) connected by electrode leads to two pre-gelled (Ag/AgCl) disposable Ambu BlueSensor wet-gel ECG electrodes attached beneath the right clavicle and left ribcage. The 48-h ECG recording will be imported to the Kubios HRV Premium V3.4.1 software [24], partitioned into 5-min segments, visually inspected to allow for manual correction of ectopic beats, detrended, and subject to Kubios’ automatic artifact correction algorithm [25]. Heart rate variability will be indexed using the time-domain metric *root mean square of successive RR differences* (*RMSSD*) given that it is less affected by breathing and a better suitable outcome measure in ambulatory studies than frequency-domain measures [26].

Following recommendations for the detection of circadian rhythmicity [27], 5-min segments across 24 h of recording will be subject to a cosinor analysis using the Cosinor package for R. Two individual-level cosine function parameters will be estimated by linear models with ordinary least square estimations to quantify the circadian variability parameters: (i) midline estimating statistic of rhythm (MESOR), defined as the rhythm adjusted 24-h mean, and (ii) amplitude, defined as the distance between MESOR and the maximum of the cosine curve (i.e., half the extent of rhythmic change in a cycle).

